### INVEST safety considerations

Patients undergoing INVEST-guided therapy will have two radiological procedures (whole-gut transit study and evacuation proctography) using ionising radiation as outlined above. The combined dose of these procedures (~1.2mSv) is equivalent to less than 7 months annual background radiation dose from living in the UK (this has been recertified by Barts Health NHS Clinical Physics Department based on doses from 20 equivalent procedures). Further, these investigations would be carried out in routine clinical practice in many centres for patients at the same point as recruitment to this study.

### Insurance and indemnity

In the event that something does go wrong and patients are harmed during the research and this is due to someone’s negligence then they may have grounds for legal action against the sponsor QMUL, but they may have to pay their legal costs. Insurance and indemnity is provided by the sponsor.

### Safety reporting

Serious adverse events (SAEs) that are considered to be “related” and “unexpected” are to be reported to the sponsor within 24 hours of learning of the event and to the REC within 15 days in line with the required timeframe. The CI will send the Annual Progress Report to the REC and to the sponsor.

#### Expected SAEs

The following SAEs are expected to occur rarely in this patient population and will not be reported:Hospital admission for exacerbation of constipation symptoms including impactionHospital admission for unrelated elective surgical procedures or accidental injuryProlongation of hospitalisation due to complications from surgery

#### Urgent safety measures

The CI may take urgent safety measures to ensure the safety and protection of the clinical trial subjects from any immediate hazard to their health and safety. The measures should be taken immediately. In this instance, the approval of the REC prior to implementing these safety measures is not required. However, it is the responsibility of the CI to inform the sponsor and Main Research Ethics Committee (via telephone) of this event immediately.

The CI has an obligation to inform both the REC in writing within 3 days, in the form of a substantial amendment. The sponsor (Joint Research Management Office (JRMO) for QMUL) must be sent a copy of the correspondence with regards to this matter.

#### Overview of the safety reporting responsibilities

The CI/PI has overall responsibility for oversight of pharmacovigilance. The CI/PI has a duty to ensure that safety monitoring and reporting is conducted in accordance with the sponsor’s requirements (see Additional file 6).

## Monitoring and auditing

### Risk assessment

The PCTU quality assurance manager will conduct a study risk assessment in collaboration with the CI. Based on the risk assessment, an appropriate study monitoring and auditing plan will be produced according to PCTU SOPs. This monitoring plan will be authorised by the sponsor before implementation. Any changes to the monitoring plan must be agreed by the PCTU QA manager and the sponsor.

A study may be identified for audit by any method listed below:A project may be identified via the risk assessment process;An individual investigator or department may request an audit;A project may be identified via an allegation of research misconduct or fraud or a suspected breach of regulations;Projects may be selected at random. The Department of Health states that Trusts should be auditing a minimum of 10% of all research projects;Projects may be randomly selected for audit by an external organisation.

Internal audits may be conducted by a sponsor’s or funder’s representative.

### Quality assessment of LVMR

Monitoring and quality control will be conducted remotely via video submission and assessed against the standardised LVMR protocol and assessment criteria (see Additional file 7). Monitoring will take the form of planned, random and triggered sessions.

#### Planned monitoring

All PIs must record and submit the unedited and anonymised video of the LVMR performed in the first patient enrolled in the CapaCiTY study 3. Each video will be allocated to two peer reviewers of a three-member expert panel. Based on blinded assessment of unedited and anonymised videos by expert review, the panel will decide whether the PI is “adherent” to the standardized technique. Any disagreement will be solved by consensus after consulting a third independent expert. If deemed “non-adherent” to the standardized technique, the site will be notified that a step needs to be corrected. The PI must submit the unedited and anonymised video of the LVMR performed in the second patient enrolled in the CapaCiTY study 3. In case of “failure” to comply with the standardized surgical technique for LVMR or following a second judgment of “non-adherence” to the standardized technique, this will trigger an on-site training and monitoring session for the site. Monitoring will continue until adherence is achieved. Otherwise a third “non-adherence” or second “failure” judgement will result in withdrawal of the site/PI from the study.

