### Specific study rationale

The overall rationale is to address the main objectives (see below) within a controlled trial. We have used a stepped-wedge, randomised trial design which permits observer-masked data comparisons between patients awaiting intervention with those who have undergone surgery. Contrary to most stepped-wedge trials individual patients are randomised rather than clustered. In brief (more detail below), eligible participants based on clinical evaluation and radio-physiological investigations (INVEST) will be randomised to three arms with different lengths of delay before surgery (see Additional file 2). In all arms there will be a period of 4 weeks post-eligibility to arrange the logistics of surgery (time (T)–4 weeks to T0) and ensure that patients have returned to their normal life routine after various assessments. LVMR will be performed at T0 in group I; T12 (12 weeks) in group II and T24 (24 weeks) in group III. Unavoidably, participants will be aware when surgery is undertaken: this, however, fortuitously meets the assumptions of the stepped-wedge design, i.e. no effect of treatment is expected until surgery has been performed. Efficacy outcome data will be collected at equally stepped time points (T0, 12, 24, 36 and 48 weeks).

This is, in effect, a modification of a standard, parallel-arm, wait-list control design, but with several advantages. First, a stepped-wedge design is more efficient and thus improves recruitment feasibility (the bane of nearly all surgical trials). Despite the multicentre approach of this study, the problems of recruitment cannot be underestimated. Simulation demonstrates that a parallel-arm design requires a much larger sample size than that proposed for the current study at the same power. Secondly, the trial design means that there is only a one in three chance (rather than one in two for a parallel arm) of waiting 6 months for surgery, which is more acceptable to patients.

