### Risks and benefits of participation

The risks of trial participation are considered very low over and above standard surgical risks. The intervention proposed is already offered to patients in specialist centres throughout the UK and internationally. The only difference conferred by participation is that the intervention will be randomly allocated by time and very carefully assessed. CC is a chronic condition (especially by the time conservative treatments have failed) and thus allocation to waiting times of up to 24 weeks poses no clinical risk. Radio-physiological tests (INVEST) are required to select patients with appropriate structural pelvic-floor problems for surgery. These would be performed in routine clinical practice in all patients undergoing LVMR and will also be mandated for the trial using specified techniques and equipment. While this may lead to slight variance from normal practice, the fundamental tests and their safety remain unchanged. Such tests have been performed daily in most specialist centres for up to 30 years without any recorded complication (Barts Health experience is over 10,000 patients). A small ionising radiation dose is required for two tests (covered below). A number of questionnaires contain personal questions about bowel problems and the effect of these on QOL and psycho-behavioural functioning; however, all have been used in studies of similar patients previously. The design of the study requires data collection at time points additional to those required for the analysis of the primary and secondary endpoints. However, this streamlines the logistics and management of the study participants through the course of the study whilst ensuring blinding is maintained and eliminating observer bias. This small additional burden on participants has been carefully balanced against the obvious benefits of the design and efficiencies of sample size gained, reducing the overall number of participants required to undergo surgery.

The benefits of participation are that patients will receive a very high standard of surgery (the most experienced UK surgeons will be participating). Further, by design, the fidelity of surgical technique will be standardised and tightly scrutinised (including by preceptorship and mentorship if required); they will also receive a high standard of monitored care as a consequence of the detailed protocol.

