## Design/methods

This is a stepped-wedge, randomised trial of LVMR in adults with chronic constipation (*n* = 114), which follows the “Standard Protocol Items: Recommendations for Interventional Trials” (SPIRIT) guidelines (see Additional file 3). Participants will be randomized to three equal arms (*n* = 38) with different lengths of delay before surgery. LVMR will be performed at T0 in group I; T12 (12 weeks) in group II and at T24 (24 weeks) in group III.

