#### Visit 2 - run-in for surgical interventions

Participants will be randomized (at visit 1) to three arms with different lengths of delay before surgery. In all arms there will be a period of 4 weeks post-eligibility to arrange the logistics of surgery (T–4w to T0) and ensure that patients have returned to their normal life routine after various assessments. Subsequently, LVMR will be performed at T0 in group I (visit 2); T12 (12 weeks) in group II (visit 3) and T24 (24 weeks) in group III (visit 4).

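### The planned surgical video review follows order of enrolment, but the randomised delay sets order of surgery, so the first video can come late and the repeat video can show an operation done before any feedback

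*Protocol article*

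**What the plan says.** The protocol article, under Planned monitoring, asks every PI for the "video of the LVMR performed in the first patient enrolled in the CapaCiTY study 3". Two members of a three-member panel judge it. If the verdict is non-adherent, the site is told which step to correct, and then: "The PI must submit the unedited and anonymised video of the LVMR performed in the second patient enrolled in the CapaCiTY study 3". A second non-adherent verdict triggers on-site training and monitoring. A third, or a second failure, leads to withdrawal of the site or PI. Because every PI must submit, I read first and second enrolled as counted separately for each PI.

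The date of surgery is set elsewhere. Design/methods states that "LVMR will be performed at T0 in group I; T12 (12 weeks) in group II and at T24 (24 weeks) in group III". The Visit 2 section adds that "In all arms there will be a period of 4 weeks post-eligibility to arrange the logistics of surgery". Allocation is equal across the three arms, with randomisation at visit 1.

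Nothing under Planned, Random or Triggered monitoring makes other trial operations at the site wait for the first verdict. The section on risks and benefits tells readers that "the fidelity of surgical technique will be standardised and tightly scrutinised".

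**The concern.** A rule based on enrolment order suits a trial in which everyone has surgery promptly. Here a patient enrolled first but allocated to group III has surgery 28 weeks after the start of the run-in (4 + 24). A patient enrolled later and allocated to group I has surgery after 4 weeks. Two things follow.

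- **Late first look.** Trial operations can be done at a site before the first planned video exists, so any drift in technique is found later than the monitoring scheme appears to intend.
- **Faulty corrective step.** The second-enrolled patient may already have had surgery when the first verdict arrives. The repeat video then says nothing about whether the correction was made. If it shows the same fault, it could still be counted as a second non-adherence, which triggers on-site training and moves the PI closer to withdrawal.

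**Working it through.** **The plan's own figure.** The mean wait is (0 + 12 + 24)/3 = 12 weeks, which agrees with the Discussion.

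**Inputs from the article.** Delays are 0, 12 or 24 weeks, allocated 1:1:1. The 4-week run-in is common to all arms. There are 114 patients at about 10 Trusts, so 114/10 = 11.4, or about 11 per site.

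**Assumptions, because the article does not give them.** Gaps between enrolments at a site are exponential with mean *m* weeks. Allocation is either simple or in blocks of three, treating the site as one stratum. Surgery takes place on the scheduled date; the 2-week tolerance is ignored.

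**Ordering rule.** A patient enrolled *t* weeks after the first, with delay *d*, is operated on before the first (delay *d*₁) if *t* + *d* < *d*₁. The run-in cancels.

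**Does anyone precede the first-enrolled patient? (simple allocation)**

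- First patient in group I (probability 1/3): nobody can precede.
- First patient in group II (1/3): group I patients enrolled within 12 weeks precede. Expected number: (12/*m*)(1/3) = 4/*m*.
- First patient in group III (1/3): group I patients enrolled within 24 weeks and group II patients within 12 weeks precede. Expected number: (24 + 12)/(3*m*) = 12/*m*.

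So P = (1/3)(1 − e^(−4/*m*)) + (1/3)(1 − e^(−12/*m*)), and the mean number of earlier operations is (4/*m* + 12/*m*)/3 = 16/(3*m*).

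- *m* = 4: P = (0.632 + 0.950)/3 = 0.53; mean 1.33.
- *m* = 12: P = (0.283 + 0.632)/3 = 0.31; mean 0.44.

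A simulation of 100,000 sites with 11 patients each agrees (0.528 and 0.305; means 1.33 and 0.44). It also supplies the figures for blocks of three:

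| Mean gap (weeks) | At least one operation before first planned video: simple / blocks | Mean number: simple / blocks | Two or more: simple / blocks |
|---|---|---|---|
| 2 | 62% / 67% | 2.4 / 2.7 | 53% / 61% |
| 4 | 53% / 62% | 1.3 / 1.6 | 36% / 44% |
| 8 | 39% / 51% | 0.7 / 0.9 | 18% / 24% |
| 12 | 31% / 42% | 0.4 / 0.6 | 10% / 15% |
| 24 | 18% / 26% | 0.2 / 0.3 | 3% / 5% |

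The ceiling is 2/3, the chance that the first patient is not in group I. Given that the first patient is in group III, the mean is 3.0 to 1.0 (simple) or 3.6 to 1.4 (blocks) for gaps of 4 to 12 weeks.

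**Does the second-enrolled patient precede the first?** The first patient's delay must exceed the second's by 12 weeks with an enrolment gap under 12, or by 24 weeks with a gap under 24.

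- Simple: of nine equally likely pairs, two differ by 12 in this direction and one by 24. P = (2/9)(1 − e^(−12/*m*)) + (1/9)(1 − e^(−24/*m*)). For *m* = 4: 0.211 + 0.111 = 0.32. For *m* = 12: 0.140 + 0.096 = 0.24.
- Blocks of three: the two patients share a block, so there are six equally likely pairs. P = (2/6)(1 − e^(−12/*m*)) + (1/6)(1 − e^(−24/*m*)). For *m* = 4: 0.317 + 0.166 = 0.48. For *m* = 12: 0.211 + 0.144 = 0.35.

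These are lower bounds for the repeat operation preceding the verdict, because the panel's review time comes on top.

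**The case against.** The strongest reply is that the planned video is not the first gate. Study setting requires at least 50 previous procedures and an independent assessment of adherence. The intervention section requires sign-off of every surgeon, with preceptorship where needed. Random monitoring adds one patient in five at site level, and that could fall early. A reader might infer from the enrolment rule that trial patients are operated on before any check of technique; the article does not support that.

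Nor is it right that a correction can never be tested. Planned monitoring goes on until adherence is reached, so a repeat video recorded too early delays the test and does not abolish it. A reader might also infer that several operations usually come first. The overall means are only about 0.4 to 1.6 for gaps of 4 to 12 weeks.

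The faster accrual rates can also be questioned. From the first enrolment (21 March 2016) to publication (5 February 2018) is about 98 weeks, and recruitment was still open. Had ten sites been open throughout and just reached 114, the mean gap would be 98 × 10/114 = 8.6 weeks. That favours the slower half of the range, although staggered site opening would shorten the gaps.

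Finally, the monitoring plan, the operating procedure and the additional file on quality assessment are not shown and may define the first patient differently. The article itself, however, says enrolled twice, and it uses the same phrase in the ordinary sense when it dates the first enrolment against registration.

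All this narrows the point. Pre-trial sign-off does not replace the in-trial review that the plan chose to add, and random review neither guarantees an early look nor repairs the corrective step.

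**Conclusion.** The point holds as a mismatch between the monitoring rule and the randomised surgery schedule. With assumed mean enrolment gaps of 12 to 4 weeks, one or more trial operations precede the first planned video at about 31-53% of sites (simple allocation) or 42-62% (blocks of three). The second-enrolled patient is operated on before the first at 24-32% or 35-48%. At a 24-week gap the first figure is still 18-26%. Accrual rate and block size are assumptions, so these are ranges and not estimates for this trial.

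The consequence is a later check of fidelity, and a repeat video that may show pre-feedback surgery and be held against the PI. It might be inferred that the randomised comparison is compromised. The documents do not support that: it would need a pre-assessed surgeon to be non-adherent, and nothing in the article lets one quantify it. The sample size and the primary analysis are unaffected. This is a cheap improvement worth making.

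**What to change.** Under Planned monitoring, replace the first patient enrolled with *the first trial LVMR performed by the PI*, and the second patient enrolled with *the next trial LVMR performed by the PI after the panel's verdict*. Leave the panel, the number of planned videos and the escalation steps as they are, and carry the same wording into the monitoring plan.

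The number of a PI's trial operations before the first planned video is then zero by construction, whatever the accrual or allocation, and the repeat video always follows feedback. The cost is a few words. The only practical demand is that recording is ready for each PI's first trial operation. No added statement on follow-up at withdrawn sites is needed for this change.

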#### Random monitoring

All PIs must record and submit the unedited and anonymised video of the LVMR performed in a randomly selected patient enrolled in the CapaCiTY study 3 (one in five at site level). The adherence to the standardized technique will be established by consensus as described for the planned monitoring.

#### Triggered monitoring

The DMC will review the morbidity and mortality rates, adverse and serious adverse events from all sites. Safety concerns may trigger additional monitoring or on-site training and mentorship visits by an expert panel. Repeated “non-adherence” or “failure” to comply will result in PI and site withdrawal.

## Devices and licenses

### Devices

The following is a list of all devices used. None are specific to the research itself and all are currently used in routine clinical practice. All are European-conformity (CE)-marked and approved for use in the UKDisposable proctoscope (supplier as in local NHS practice). This will be commonly be used as part of clinical examination at baseline and is also used to introduce barium paste into the rectum during INVEST;High-resolution anorectal manometry catheters and rectal balloons for anal manometry/rectal sensory testing: various suppliers (part of INVEST – see above);Balloon catheters for the balloon expulsion test (part of INVEST – see above);Radiopaque markers for colonic transit study: various suppliers (part of INVEST – see above);Standard departmental x-ray equipment including the radiolucent commode for the proctogram (part of INVEST- see above);Surgical instrumentation including disposable and reusable instruments;Mesh:Synthetic: titanium-coated lightweight polypropylene;Biologic: Strattice, Permacol;Mixed: biologic and synthetic;Suture material: any; usually long-term absorbable material e.g. PDS.

### Licenses

Most of the questionnaire-based tools are free to use within the public domain. The permissions/licenses to use all instruments will be sought with finance where required:PAC-QOL score: MAPI registeredPAC-SYM score: MAPI registeredMSHQ-EjD: MAPI registeredEQ-5D-5L: registered

No costs are associated with the following tools:Depression, anxiety and somatisation modules of the Patient Health QuestionnaireIllness perception questionnaireComposite Rome III/Cleveland Clinic constipation questionnaireBrief, chronic pain, autonomic and joint hypermobilityNegative perfectionismAvoidant and “all or nothing” behaviour subscales of the behavioural response to illness questionnaire

## Trial management

Each participating centre will identify a site-specific PI who will nominate a local contact for that centre (this may be the PI). The PI and local contact will:Be familiar with the trial;Liaise with the Programme Management Group (PMG);Ensure that all staff involved in the trial are informed about the trial and have received requisite training;Ensure that mechanisms for recruitment of eligible participants, including the availability of participant information and data collection tools, are in place;Monitor the effectiveness of data collection tools and participant information and discuss the reasons for non-recruitment with relevant staff;Ensure site staff collect necessary trial data and perform quality checks;Notify the CI of any SAEs and serious breaches within required timelines;Make data available for verification, audit and inspection processes as necessary;Respond to requests for documentation and data required for centralised monitoring;Ensure that the confidentiality of all information about trial participants is respected by all persons.

Site initiation will be conducted with each site. This will include training in the trial protocol and SOPs, such as data collection, randomisation and taking informed consent. Evidence of appropriate training, local approvals and essential documentation will be required before participants are enrolled at each site. Training will be documented on training logs.

### Trial committees

The project will be under the auspices of the CI and the PCTU. The project will be overseen by a Programme Steering Committee (PSC). The composition and responsibilities of the PSC will comply with the NIHR guidance and PCTU SOP on Trial Oversight Committees. The role of the PSC is to provide overall supervision of the study on behalf of the sponsor and funder to ensure the study is conducted in accordance with the principles of Good Clinical Practice (GCP) and relevant regulations.

The responsibilities of the PSC will include:Ensuring that views of users and carers are taken into considerationAdvising on the trial protocolAdvising on changes in the protocol based on considerations of feasibility and practicabilityAssist in resolving problems brought to it by the PMGMonitor the progress of the trial and adherence to the protocol and milestonesConsider new information of relevance from other sourcesConsider and act on the recommendations of the DMEC, sponsor and/or RECReview trial reports and papers for publication

The PSC will meet to review the protocol before the start of the programme and then soon after the first participants are recruited and either meet or teleconference every 6 months thereafter throughout the lifetime of the programme. Representatives of the trial sponsor and funder will be invited to attend.

The PMG will meet monthly initially during study set up and then less frequently, every 2 months. The PMG will be responsible for day-to-day project delivery across participating centres, and will report to the PSC. The PMG will be responsible for monitoring adherence to the study timelines and expected recruitment rates. Regular reports will be produced to enable deviations from the project plan to be identified and contingencies planned, discussed and executed in a timely fashion (see Additional file 8).

The DMEC will be convened. A “Data Monitoring Committees: Lessons, Ethics, Statistics” (DOMACLES) charter will be adopted, and the project team will provide the DMEC with a comprehensive report, the content of which should be agreed in advance by the Chair of the DMEC and follow guidelines set out in the charter. The DMEC will meet at least 4 weeks prior to the PSC to enable recommendations to forwarded.

A constipation research advisory group (CRAG) will be formed as part of a well-developed patient and public involvement (PPI) strategy at QMUL (in close association with the charity Bowel and Cancer Research). This advisory group will comprise eight patients and two lay members from London and Durham. This group will have geographical diversity (north and south) and a disease-appropriate demographic (eight women, two men). The CRAG will review participant information sheets, booklets, diaries and advertising/marketing materials, provide lay representation on the PSC, conduct parallel qualitative analysis, produce lay summaries for dissemination of results, present at local research events and conduct patient focus groups and workshops.

